### Study sample size

Taking into account that the EB rate in Andalusia is 25%, this is considered the expected value in the control group. An estimated increase effect of 12% of the EB rates at 6 months is established, as asserted in previous studies [34]. To reach this difference between both groups, a two-tail hypothesis is set out, with a power of 80% and assuming a type I error of 5%, assuming a loss of 10% in the follow-up, the necessary sample increases to 512 women, 256 in each group. Missing values in the follow-up will be addressed by multiple imputation technique, performing attrition analysis.

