Should any statistically significant differences be considered, confidence intervals at 95% for mean differences will be determined. For the comparison of numerical variables between more than two groups, and once the independence, normality, and homoscedasticity requirements are validated, the ANOVA (analysis of variance) test will be conducted; in case the requirements are not achieved, the Kruskal-Wallis’ test will be carried out. Should any statistically significant differences between the means of the different studied sub-groups be detected, multiple comparison tests will be conducted in order to identify between which sub-groups were those differences found, considering a corrected level of alpha significance based on the number of comparisons made. On the survival analysis, the Kaplan-Meier’s non-parametric estimator will be used.

The effectiveness analysis will be conducted through the comparison of the number of women who chose to breastfeed exclusively at 6 months in both groups, using Fisher’s exact test and estimating the confidence intervals of the difference. Should factors be unequal in both groups, an explanatory logistic regression model would be carried out, in which the dependent variable would be exclusive breastfeeding, and the independent one would be the intervention group, adjusted for the potential factor findings. The efficacy analysis would be carried out on an intention-to-treat basis.

In order to avoid the effect of the intervention on the duration of breastfeeding in the support group, a survival analysis will be conducted, which will compare the intervention and control groups using the log-rank test. Control of potential confounders will be made through Cox’s different regression models. All *p* values under 0.05 will be considered as statistically significant.

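### The stated 80% power does not belong to the stated primary test: Fisher's exact test gives about 77% at the planned evaluable sample even if women were independent, and less once centres are allowed for

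*Protocol article*

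**What the plan says.** Protocol article, Study sample size:

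- Control rate: "Taking into account that the EB rate in Andalusia is 25%, this is considered the expected value in the control group".
- Effect: "An estimated increase effect of 12% of the EB rates at 6 months is established".
- Error rates: "a two-tail hypothesis is set out, with a power of 80% and assuming a type I error of 5" per cent.
- Size: "assuming a loss of 10% in the follow-up, the necessary sample increases to 512 women, 256 in each group".
- Missing data: "Missing values in the follow-up will be addressed by multiple imputation technique, performing attrition analysis".

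The section names no sample-size formula and no design effect.

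Protocol article, Analysis: the test fixed for the effectiveness analysis is worded as "using Fisher’s exact test and estimating the confidence intervals of the difference". What it is applied to, according to the same sentence, is the "comparison of the number of women who chose to breastfeed exclusively at 6 months in both groups". Logistic regression enters only if factors turn out unequal between the groups. The same section makes health centres the units of randomisation and the mother-newborn dyad the unit of analysis.

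**The concern.** Power belongs to a particular test on a particular number of analysed women. The article fixes both the power and the test, so this is not a detail left to the analysis plan.

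Fisher's exact test is more conservative than the uncorrected chi-square test that the usual two-proportion formula describes. A size taken from that formula will therefore fall short of its nominal power when Fisher's test is used. At stake is a risk of missing the target effect that is higher than the 20% stated. The shortfall grows once outcomes within a centre are correlated, because neither the size nor the test allows for centre.

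**Working it through.** **Inputs.** From Study sample size: control rate 0.25; increase 0.12, so 0.37 in the intervention arm; two-sided alpha 0.05; power 0.80; 10% loss; 256 per arm. Evaluable per arm: 256 × 0.9 = 230.4, taken as 230. From Analysis: Fisher's exact test.

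The 12% is read as an absolute difference. A relative 12% (25% to 28%) would need about 3,397 per arm, which cannot give 512.

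**Step 1: reproduce 512.** Uncorrected two-proportion formula with pooled variance under the null, mean rate 0.31:

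n = [1.96 × √(2 × 0.31 × 0.69) + 0.8416 × √(0.25 × 0.75 + 0.37 × 0.63)]² / 0.12²

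= [1.96 × 0.6541 + 0.8416 × 0.6485]² / 0.0144 = 232 per arm.

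| Formula | Per arm before loss | Per arm after 10% loss |
|---|---|---|
| Uncorrected, pooled | 232 | 256 (× 1.1) or 258 (÷ 0.9) |
| Uncorrected, unpooled | 229.3 | 255 (÷ 0.9) |
| Arcsine | 231.2 | 257 (÷ 0.9) |
| Continuity-corrected (close to Fisher) | 249 | 274 (× 1.1) or 277 (÷ 0.9) |

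The uncorrected variants all land at or close to 256. The continuity-corrected one gives 548 or 554 in total and does not reproduce 512.

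**Step 2: power of the named test, women independent.** For every pair of counts (x, y), the product of the two binomial probabilities is summed over those tables whose two-sided p-value is at most 0.05.

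| Evaluable per arm | Fisher's exact | Uncorrected chi-square |
|---|---|---|
| 230 (the planned 10% loss) | 77.0% | 79.8% |
| 247 | 79.9% | 82.5% |
| 248 | 80.2% | 82.7% |
| 256 (no loss) | 81.5% | 83.9% |

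At 230 the chi-square test is within 0.2 points of 80%, so the choice of test, not rounding, explains nearly all of the gap. Fisher's test first reaches 80% at 248 evaluable per arm: 248 ÷ 0.9 = 276 per arm, or 552 in total.

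**Step 3: type I error, women independent.** With 25% in both arms and 230 per arm, Fisher's test rejects 3.9% of the time.

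**Step 4: what clustering does.** The article gives no intra-centre correlation, cluster size or number of centres, so the design effects below are assumptions. For a test that allows for centre, the effective size is 230 ÷ design effect, and the Step 1 formula gives:

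| Assumed design effect | Effective women per arm | Power |
|---|---|---|
| 1.0 | 230 | 79.7% |
| 1.2 | 192 | 72% |
| 1.5 | 153 | 62% |
| 1.95 | 118 | 51% |

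If Fisher's test is kept and centre ignored, its rejection limit stays put while the true variance grows. A size of 3.9% corresponds to a limit of about 2.06 standard errors. At an assumed design effect of 1.5 this becomes 2.06 ÷ √1.5 = 1.68, a true type I error of about 9%. Its power falls as well: 77.0% corresponds to a normal deviate of 0.74, and 0.74 ÷ √1.5 = 0.60 gives about 73%.

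**The case against.** **The arithmetic is right and the gap is small.** The stated 512 does follow from the stated inputs, and the section does not say which test its power refers to. A reader might infer a calculation error, but there is none: the formula and the test simply do not match. The gap is about 3 points, and rounded planning values move power as much. At 230 per arm, Fisher's test has 80.2% power for 25% against 37.5%, and 74.6% for 28.5% against 40.5%, the first of these being the national figure in the Discussion. This stands as a limit on the size of the point. It does not make the stated power true for the stated inputs.

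**With imputation, 256 per arm are analysed.** Nominally so, and with no loss Fisher's test would have 81.5%. But the plan itself assumes 10% loss, and multiple imputation does not in general restore lost information. What stands is that 77% must not be called an unconditional best case.

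**Fisher's test is at least safe.** From the 3.9% a reader might infer that the test is merely cautious. That figure needs independent women. Under randomisation by centre, a test that ignores centre can exceed 5%.

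**Clustering matters more.** It does. Under the assumed design effects it costs far more than 3 points, and recruiting 552 women for Fisher's test would not mend the design. That decides the remedy; it does not remove the mismatch, which exists with no clustering at all.

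**Conclusion.** The point holds. On the article's own inputs (25% against 37%, two-sided 5%, 230 evaluable per arm), the named primary test has about 77% power under independence, not 80%. The chance of missing a true 12-point effect is about 23%. Taken alone, the shortfall is modest.

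The 77% assumes the full 10% loss, no recovery of information by imputation, and independent women. It is not the power of this trial. With centres as the units of randomisation, as the Analysis section states, any positive within-centre correlation lowers the power. How far cannot be fixed from the article, because no correlation or cluster size is given. For the same reason, the article supports saying that the type I error of Fisher's test may exceed 5%, but not by how much.

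**What to change.** 1. **Analysis.** Replace Fisher's test for the primary comparison with an analysis that accounts for centre: a mixed logistic model or GEE with centre as the cluster, with a small-sample correction if centres are few.
2. **Study sample size.** Restate the power of the existing 512 women for that analysis over a stated range of assumed intra-centre correlations and cluster sizes. Note that about 77% is the figure for Fisher's test under individual randomisation with 10% loss.

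Printing 77% while keeping Fisher's test is not enough, since that figure does not describe a centre-randomised trial. No extra recruitment is asked for. The cost is a short change in each of the two sections and a less favourable stated power.

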#### Secondary outcomes measurement

Differences between both groups with respect to the following:
***Sociodemographic outcomes:*** mother’s age, schooling level (without any studies, primary, secondary, University studies), marital status (single, married, divorced, widow), work status (self-employed, employed, unemployed), occupation, working hours/week, home country.***Breastfeeding outcomes:****Breastfeeding observation form (BREAST):* it is a tool developed by a WHO experts committee in 1992 [24], which collects the key points in order to assess a breastfeed through observation: body position (B), responses (R), emotional bonding (E), anatomy (A), suckling (S), and time spent suckling (T). In the Baby-Friendly Hospital Initiative (BFHI) strategy [27], it is specified that a complete breastfeed observation by an expert is essential for checking whether there is an appropriate transfer and for diagnosing the cause of possible difficulties, should there be any, for further resolution.*Breastfeeding Self-Efficacy:* a reduced version of the *Breastfeeding Self-Efficacy Scale-Short Form* (BSES-SF) [30] scale [26] which was validated in Spanish by Oliver-Roi et al. [26], and counts on 14 items grouped in only one dimension. It is a one-dimensional, self-completed scale of 14 items, positively presented and preceded by the sentence ‘I always can’. For scoring, it has a Likert-type scale from 1 to 5, where 1 indicates ‘not sure at all’ and 5 indicates ‘very sure’. Higher scores mean higher self-efficacy levels for breastfeeding. The BSES-SF Spanish version’s reliability, measured with the Cronbach alpha coefficient, is 0.92. It is a valid and reliable measure, successfully adapted into diverse cultural contexts, including the Spanish [26, 31].*Previous breastfeeding experiences*: multiparous women will be asked about their experience with breastfeeding while raising previous children, as well as the reason for giving it up.*Type of infant feeding after hospital discharge*: exclusive breastfeeding, nearly exclusive breastfeeding, partial breastfeeding, formula feeding.*Common breastfeeding problems and solutions* (consultation with the midwife, Internet, social networks, reference person …).*Reasons for breastfeeding interruption:* mother’s decision, low weight gain, mother’s disease, newborn’s disease, contraindication due to medication, nipple problems, difficulties with the technique, return to work, etc.***Obstetric outcomes:*** mode of birth (eutocic/dystocic/C-section), mode of start of labour (spontaneous/induced), analgesia during labour (epidural/others), perineal trauma classification (episiotomy/perineal tear degree), initiation of skin-to-skin contact immediately after birth.***Neonatal outcomes:****Perinatal aspects*: newborn’s gender (female/male), weight (expressed in grams), Apgar test score [32], admission in neonatal care unit (yes/no).*Newborn’s health problems in the first 6 months of life:* description for subsequent coding.***Behaviour outcomes:****General Self-Efficacy*: this scale assesses optimistic self-beliefs of coping efficiently with a variety of difficult demands in life. Baessler and Schwarzer’s adaptation [33] will be used, although, in spite of its original format, a ten point Likert-type answer scale suggested by Sanjuan et al. [25] will be used, consisting of 10 items and a scoring range from 10 to 100, with an internal consistency of 0.87 (Alpha coefficient) and a correlation between two halves of 0.88.***Outcomes related to the use of social networks for support:*** frequency of use of social networks and/or WhatsApp, number of times the resource is used, questions resolved through face-to-face appointment in the midwife clinic, use of the App for consultation regarding breastfeeding.

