### Analysis

A complete statistical analysis plan will be previously performed, as well as a report thereof and of the results, according to the Consolidated Standards of Reporting Trials (CONSORT) [35, 36]. The analysis will be carried out on the basis of an intention-to-treat principle, without taking into account whether or not adherence to the breastfeeding support group was completed. Individual health centres are the randomization units and the mother-newborn dyad will be the analysis unit. All statistical trials and confidence intervals will be assumed with a type I error established in alpha = 0.05, using the IBM SPSS V22 statistics package [37].

An exploratory data analysis will be conducted in order to identify atypical values, for the total of our studied sample, as well as for the different sub-groups created. A graphic exploratory analysis of the different studied variables will also be conducted, according to their numerical or non-numerical character. Frequency and percentage distribution scales will be elaborated for the descriptive analysis of variables with a qualitative (non-numerical) character. For the quantitative (numerical) ones, centralization and dispersion measures will be calculated. In variables with a normal distribution, the mean and the standard deviation will be calculated and, in those with an asymmetric distribution, the mean and interquartile range (p25-p75) will be calculated. Furthermore, point estimators and confidence intervals will be calculated at 95% for averages and percentages. The relationship between two qualitative variables will be analysed with Pearson’s chi-square test, the correction for continuity of the chi-square test, a linear-by-linear association test, and Fisher’s exact probability test, based on the application criteria. The significant results of these tests will be complemented with a confidence interval set at 95% for percentage differences.

Regarding the numerical variables between two groups, the Student’s t-test of independent samples for mean comparisons will be carried out, once the requirements of randomness, normality (Kolmogorov-Smirnov’s test, or Shapiro-Wilks’ test, according to the sample size) and equality of variances (Levene’s test) are validated. In case this one is not achieved, the Student’s t-test for independent samples with Welch’s correction will be carried out. In case normality requirements are not accomplished, the Mann-Whitney’s U test will be applied.

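### The adjusted model for 6-month exclusive breastfeeding is run only if groups look unequal, with covariates chosen from the data, and secondary differences get an interval only when significant

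*Protocol article*

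**What the plan says.** All the analysis rules below stand in the protocol article, Analysis section.

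- **Primary comparison.** EB at 6 months is compared between groups "using Fisher’s exact test and estimating the confidence intervals of the difference". No covariate enters, and the interval has no significance condition.
- **Adjusted model.** It is conditional: "Should factors be unequal in both groups, an explanatory logistic regression model would be carried out". The model has EB as the dependent variable and group as the explanatory one, "adjusted for the potential factor findings". No criterion for inequality and no covariate list are given.
- **General categorical comparisons.** "The significant results of these tests will be complemented with a confidence interval set at 95% for percentage differences".
- **General numerical comparisons.** "Should any statistically significant differences be considered, confidence intervals at 95% for mean differences will be determined".
- **Descriptive intervals.** Without condition, "point estimators and confidence intervals will be calculated at 95% for averages and percentages".
- **Survival analysis.** Confounders are handled in Cox models, with no imbalance condition and no named covariates.

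Under Secondary outcomes measurement, sociodemographic, obstetric and perinatal variables appear in a list introduced by "Differences between both groups with respect to the following". Table 1 records them at baseline, together with previous breastfeeding experience. The Background names maternal age, schooling, family support, multiparity and antenatal lessons as factors in how long breastfeeding lasts, and experiences with previous births as another influence.

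**The concern.** Two rules let the observed data decide what is reported.

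The first concerns the primary outcome. Imbalance is a poor way to choose covariates. It picks up factors that differ by chance even if they have no bearing on EB, and passes over strong predictors that happen to be balanced. When the model does run, a second estimate appears whose covariates were chosen after seeing the data, and the protocol does not say how to read the result if the two differ. The odds ratio also changes meaning once a prognostic covariate enters, so the adjusted and crude figures are not interchangeable even under perfect balance.

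The second concerns the secondary comparisons. If an interval for the difference appears only after p<0.05, a non-significant result cannot be read as either a small effect or an imprecise one. The differences that do carry intervals are a selected set that tends to overstate the effect.

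**Working it through.** **1. The plan's own figure.** Inputs from Study sample size: control 25%, increase 12% (read as percentage points, so 37%), two-sided 5%, power 80%, loss 10%.

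n per arm = [1.960·√(2·0.31·0.69) + 0.842·√(0.25·0.75 + 0.37·0.63)]² / 0.12² = 232.

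232 × 1.10 = 255.2, rounded up to 256, or 512 in total. The stated figure reproduces. Dividing by 0.90 instead gives 258 per arm, 516 in total. With 230 completers per arm, power is 79.7%.

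**2. How often chance alone fires the trigger.** Assumptions, not in the protocol: unequal means p<0.05, and the k factors are independent. P(at least one) = 1 − 0.95^k.

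| Factors k | Chance of at least one |
|---|---|
| 5 | 23% |
| 10 | 40% |
| 15 | 54% |
| 20 | 64% |

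Positive correlation between factors lowers these values. Tests on individual women when centres were randomised raise them.

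**3. What planned adjustment would gain for EB.** The protocol gives no covariate strength, so a range is assumed. Simulation: 230 per arm, 25% versus 37%, one standard-normal baseline score, no clustering, 1,500 trials per row, Wald tests from logistic models. The simulation error of each power is about √(0.8·0.2/1500) = 0.01.

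| Log-odds per SD | SD of risk difference, crude → adjusted | Power, crude → adjusted | Mean log odds ratio, crude → adjusted |
|---|---|---|---|
| 0 | 0.0429 → 0.0430 | 0.81 → 0.82 | 0.581 → 0.582 |
| 0.5 | 0.0436 → 0.0426 | 0.80 → 0.82 | 0.568 → 0.599 |
| 1.0 | 0.0430 → 0.0393 | 0.81 → 0.88 | 0.576 → 0.682 |

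A worthless covariate costs nothing visible, a moderate one gains little, and a strong one gains something useful. The last column shows the change in meaning of the odds ratio: at 1.0 per SD it moves from exp(0.576) = 1.78 to exp(0.682) = 1.98 on average.

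**4. What reporting intervals only after significance does.** Simulation of a secondary percentage difference with 230 per arm and control 25% (illustrative values, no clustering).

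| True difference | Share significant | Mean difference among significant results | Coverage of their 95% intervals |
|---|---|---|---|
| 0.12 | 80% | 0.135 | 96.7% |
| 0.06 | 30% | 0.108 | 91.5% |
| 0.03 | 11% | 0.094 | 74% |

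Without the filter, coverage is about 95% throughout. At a true difference of 0.06, about 70% of results would carry no interval for the difference.

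**The case against.** The strongest defence is that the primary result is already fixed. The effectiveness analysis is the Fisher comparison with its interval, and the logistic model is labelled explanatory. The section also announces a complete statistical analysis plan, which could name the covariates. Much of this stands: the crude EB difference and interval are always produced, and a missing covariate list alone would be no finding. But the conditional rules are written in this text. An analysis plan could fill in the covariates, yet to remove the triggers it would have to contradict the protocol.

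On intervals, the unconditional descriptive ones for averages and percentages would let a reader approximate some differences. They describe quantities within groups and do not replace a reported interval for the contrast.

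Several stronger readings are tempting and not supported:

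- *All intervals depend on significance.* This is false for the primary outcome.
- *All adjustment depends on imbalance.* The Cox models carry no such condition.
- *The secondary-outcome list supplies the trigger.* One might count about 21 early-recorded variables and compute 1 − 0.95^21 = 66%. Nothing links that list to the trigger, no p-value criterion is stated, and items such as work status, occupation and working hours are plainly related. Only a range under stated assumptions is defensible.
- *The self-efficacy scales are fixed to an analysis that ignores baseline.* The sentence that "the Student’s t-test of independent samples for mean comparisons will be carried out" is a generic rule for numerical variables. The Analysis section names neither scale, and scale-specific models are commonly left to the analysis plan. A gain equivalent to 33% more women, from 1/(1 − 0.5²) at an assumed correlation of 0.5, also ignores clustering and concerns secondary scales only.

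**Conclusion.** The point holds in two limited parts. For 6-month EB, both the existence and the content of the adjusted logistic estimate depend on the data, and collected prognostic factors have no planned role in the primary comparison. For the general comparisons of secondary variables, the interval for a difference depends on significance.

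The 23% to 64% trigger range rests on a p<0.05 criterion and on 5 to 20 independent factors, neither of which the protocol states. The loss from leaving out planned adjustment is modest: about 0.02 in power at log-odds 0.5 per SD and 0.06 to 0.07 at 1.0, with assumed covariate strengths and no allowance for clustering by centre, which is a separate matter. The reason to change is mainly that the adjusted result should not be chosen after seeing the data, and only secondly precision. The wording should be corrected, but the crude primary estimate and its interval are not in doubt on this ground.

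**What to change.** 1. Replace the conditional logistic model with one prespecified adjusted EB model, run whatever the balance. Use a short list of collected factors fixed before allocation: maternal age, schooling level and previous breastfeeding experience. The Background names the first two as prognostic; the third is the collected variable closest to its multiparity and previous-birth experience. State the role of this model beside the Fisher comparison.
2. Do not adjust for feeding type at 10 days. Primary outcomes measurement lists it within the outcome, and it is recorded after allocation at 35–37 weeks in an unblinded trial. Since EB is defined from birth, it could also largely determine the 6-month result.
3. Report the sociodemographic, obstetric and perinatal variables as baseline characteristics, not as outcomes tested between groups.
4. Give the estimate and 95% interval for every between-group comparison, regardless of p.

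The cost is wording only. The covariates are already in Table 1, no new data are needed, and the sample size stays 512.

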
Table 1 shows the measurement tools used for data collection, the method of collection and time points.

**Table 1 Tab1:** Measurement domains, survey tools, and collection time point

Variable	Component	Measurement tools/ Questions	Baseline	2mth	4mth	6mth
*Sociodemographic measures*		Age, schooling level, marital status, employment, ethnicity.	✓			
*Clinical information*	Obstetric outcomes	Type of birth, onset of labour, type of analgesia, perineal trauma, skin-to-skin technique	✓			
	Neonatal outcomes	Gender, weight, Apgar, neonatology admission, health problem	✓			
*Breastfeeding measures*	Previous experience	In affirmative case, interruption motivation	✓			
	Type of breastfeeding	Exclusive breastfeeding, nearly exclusive breastfeeding, partial breastfeeding, formula	✓	✓	✓	✓
	Breastfeeding information	Breastfeeding observation form (BREAST)	✓			
	Breastfeeding Self-Efficacy	Breastfeeding Self-Efficacy Scale-Short Form (BSES-SF)	✓	✓	✓	✓
	Breastfeeding problems	Type of problem and resolution (midwife, peer, social network, Internet …)	✓	✓	✓	✓
	Breastfeeding Interruption - Motivation			✓	✓	✓
*Behaviour measures*	Self-Efficacy General Scale		✓	✓	✓	✓
*Social networks (intervention group)*	Use and frequency			✓	✓	✓
	Problem consulted			✓	✓	✓
*Clinical services*	Appointments related to breastfeeding attended			✓	✓	✓

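### About 16 characteristics fixed before the first support session are listed as secondary outcomes and fall under an unadjusted 0.05 rule, which also covers six self-efficacy tests

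*Protocol article*

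**What the plan says.** The section Secondary outcomes measurement opens with "Differences between both groups with respect to the following". The list under that line begins with "mother’s age, schooling level (without any studies, primary, secondary, University studies), marital status (single, married, divorced, widow), work status" and goes on to occupation, weekly hours and home country. It then includes mode of birth, start of labour, analgesia, perineal trauma and skin-to-skin contact, and later infant sex, weight, Apgar score and neonatal unit admission.

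Table 1 treats the same material differently. The sociodemographic row and the obstetric row ("Type of birth, onset of labour, type of analgesia, perineal trauma, skin-to-skin technique") are ticked in the baseline column only, and so is the neonatal row with sex, weight and Apgar. Description of the intervention places the support groups after birth, following an individual visit in the first ten days.

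On testing, the Analysis section states "All statistical trials and confidence intervals will be assumed with a type I error established in alpha = 0.05". It closes by saying that p "values under 0.05 will be considered as statistically significant". The one correction mentioned, "considering a corrected level of alpha significance based on the number of comparisons made", applies to comparisons between sub-groups after a significant overall test. The same section runs an adjusted logistic model for exclusive breastfeeding if factors turn out unequal between the arms, and gives no criterion for unequal.

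**The concern.** An outcome is something the intervention could change. Maternal schooling, country of origin, the way labour started and the sex of the infant are settled before a woman attends her first group. A between-arm difference on any of them is chance, or a product of how centres and women came into the trial. Listing them as secondary outcomes under a blanket 0.05 rule allows such a difference to be reported as a significant secondary result.

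Two further consequences follow. First, if the logistic model is triggered by significance on these items, chance helps decide whether the main result is adjusted and for what. Second, the aims include the influence of the groups on breastfeeding self-efficacy. Breastfeeding and general self-efficacy are each measured at 2, 4 and 6 months, and no scale or visit is singled out. One nominally significant result out of six could be presented as support for that aim, at an error rate above 5%.

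**Working it through.** The protocol states no error rate for the secondary comparisons, so there is no figure to reproduce.

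**Inputs**
- Per-test level: α = 0.05 (Analysis).
- Items fixed before the first session (Secondary outcomes measurement): age, schooling, marital status, work status, occupation, hours and country make 7; mode of birth, start of labour, analgesia, perineal trauma and skin-to-skin contact make 5; infant sex, weight, Apgar and neonatal unit admission make 4. Total 7 + 5 + 4 = 16.
- Self-efficacy (Table 1): 2 scales × 3 follow-up visits = 6 tests.
- Correlation between test statistics, ρ: not in the document. Assumed range 0 to 0.8.

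**Formulas**, with all null hypotheses true and women treated as independent
- Independent tests: 1 − (1 − α)^k.
- Equally correlated normal statistics: 1 − ∫ φ(x) [Φ((1.96 − √ρ·x)/√(1−ρ)) − Φ((−1.96 − √ρ·x)/√(1−ρ))]^k dx.

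**Results**
- 16 items, independent: 1 − 0.95^16 = 1 − 0.440 = 0.560. Expected number of false positives: 16 × 0.05 = 0.8.
- 6 self-efficacy tests, independent: 1 − 0.95^6 = 1 − 0.735 = 0.265.

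| Chance of at least one false p < 0.05 | ρ = 0 | ρ = 0.5 | ρ = 0.8 |
|---|---|---|---|
| 16 pre-intervention items | 56% | 37% | 21% |
| 6 self-efficacy tests | 26% | 21% | 14% |

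For items as unlike as infant sex, schooling and country of origin, low correlation is the more plausible case; at ρ = 0.2 the 16-item figure is 52%. For one scale repeated over visits, higher correlation is plausible.

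**Sensitivity to the count.** Without neonatal admission, 15 items give 1 − 0.95^15 = 54%. The seven sociodemographic items alone give 1 − 0.95^7 = 30%.

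**Clustering.** Centres are randomized, but the listed tests treat women as independent. The document gives no intracluster correlation. An assumed design effect of 1.2 raises the per-test error to 7.4%, and 16 independent tests then give 1 − 0.926^16 = 71%. The table is therefore on the low side if there is positive clustering.

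**The case against.** The strongest reply is that the protocol uses baseline differences as imbalance to adjust for. Table 1 labels these items as measures and clinical information under a baseline column, the logistic and Cox models adjust for them, and one aim is to find factors related to sustained breastfeeding. Nowhere does the text say that schooling or mode of birth will be claimed as an effect of the groups. That is right about the probable intent. It does not change the definition of the secondary outcomes, and it shows that the comparisons may steer the adjusted analysis.

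A second reply is that hierarchy and multiplicity for secondary outcomes belong in a statistical analysis plan, which the protocol announces and which is not shown. This stands in part: the absence of a ranking or gatekeeping rule is not held against the protocol. What remains is what the text itself states, namely the misclassification and the blanket threshold. The closing threshold sentence follows the survival analysis and could be read as limited to it, but the general alpha statement earlier in the section covers all tests.

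A third reply is that obstetric and perinatal events come after allocation at 35–37 weeks, and that the aims and Discussion mention antenatal sessions. The section on the intervention, however, describes antenatal care as usual care in both arms. The sociodemographic items are beyond dispute in any case. Neonatal admission is also recorded at follow-up, so only admission at birth belongs with the baseline items.

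A reader might infer that false findings across the whole secondary list are almost certain. The figures do not support this. The list has 28 items by count, and Table 1 marks the social-network items as intervention group only, which leaves 24 to compare: 1 − 0.95^24 = 71% if independent, and less with correlation. It takes 59 independent tests to reach 95%. Several items, such as problems consulted and newborn health, are also mainly descriptive. Nor does the list inflate the effectiveness conclusion, which rests on one named comparison.

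**Conclusion.** The point holds in limited form. About 16 pre-intervention characteristics are wrongly defined as secondary outcomes and fall under a rule that calls any p below 0.05 significant. At least one chance difference among them is somewhat more likely than not if the tests are close to independent (56%), and less likely than not at a correlation of 0.5 (37%). The six self-efficacy tests carry a 14–27% chance of at least one false positive. These figures assume that every null hypothesis is true, that each item is tested once at 5%, and that women are independent.

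The effect on the adjusted logistic model is conditional: it arises only if inequality is judged by these tests, which the text leaves open. Not every baseline difference need be chance. Centres are randomized without blinding and eligibility is rechecked after birth, so real imbalance is possible. That is a further reason to present these items as baseline data. The primary comparison of exclusive breastfeeding at 6 months is a single test and is unaffected by the secondary list.

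**What to change.** 1. In Secondary outcomes measurement, move the sociodemographic, obstetric and perinatal items (sex, weight, Apgar, admission at birth) and previous breastfeeding experience to baseline characteristics, described by arm without p-values.
2. In Analysis, replace the trigger based on unequal factors with covariates fixed in advance from those already collected.
3. Limit the closing significance sentence to the primary 6-month comparison, and align the general alpha statement with it. Report the other secondary comparisons, including both self-efficacy scales, as exploratory, with estimates and 95% intervals.
4. Optionally, name one key secondary, for example the breastfeeding self-efficacy score at one stated visit, tested only if the primary is significant. This is a choice, not a requirement.

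The cost is wording in the protocol and analysis plan, with no extra data or women. The small downside is that fewer secondary results can be called significant.
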